# Effects of Photobiomodulation in Children with Down Syndrome and Possible Sleep Bruxism: Protocol For A Randomized, Controlled, Blind, Clinical Trial

**DOI:** 10.1097/MD.0000000000019904

**Published:** 2020-04-24

**Keywords:** acupoints., Bruxism, children, down syndrome, low level laser therapy, photobiomodulation

## Abstract

**Objective::**

Analyze salivary levels of dopamine and cortisol and muscle activity before and after treatment with low-level laser therapy administered to acupoints in children with DS.

**Methods::**

A randomized, controlled, clinical trial will be conducted. Individuals 4 to 17 years of age with a diagnosis of DS and possible sleep bruxism will be screened at the Integrated Health Clinic of Nove de Julho University. We will evaluate orofacial dysfunction (Nordic Orofacial Test - Screening questionnaire), Masseter muscle activity during sleep will be assessed by BiteStrip and the masticatory muscles will be evaluated by electromyography (BTS TMJOINT) head posture as well as salivary cortisol and dopamine. After the evaluations, the participants will be randomized into 2 groups: Grupo 1 – treatment with low-level laser therapy at a wavelength of 808 nm; Group 2 – sham treatment (simulated laser therapy). Treatment will be conducted twice per week for a total of 12 sessions. The data will be tabulated and treated using GraphPad Prism version 7.0. The Kolmogorov-Smirnov test will be used to determine the normality of the data. Variables that fit the Gaussian curve will be expressed as mean and standard deviation. The ANOVA 2-way will be used for comparisons between the groups, with the significance level set to 5% (*P* < .05).

**ClinicalTrials registration number:** NCT04211870.

## Introduction

1

Down syndrome (DS) is genetically characterized by the total or partial presence of an extra chromosome in par 21, also known as chromosome 21 trisomy. One of the manifestations found in individuals with DS is the muscular hypotonia, especially of the masticatory and oropharyngeal muscles. Such muscles may compromise basic actions such as swallowing, breathing and speech.^[1]^ Therefore, they may present alterations in oral functions, such as delayed eruption of deciduous dentition, open or crossbite, microdontia, macroglossia and reduced oral cavity, providing oral breathing and salivary leak.^[2]^

Hypotonia, muscle weakness, sluggish motor response information, and sensory changes can impair their ability to maintain adequate muscle balance. Consequently, the movements become difficult, slow and disorganized, resulting in stress, anxiety and consequently poor quality of life. In addition, due to muscle hypotonia, children with DS tend to project their tongue, and for more stable occlusion they also project their jaw. Associated, these factors may cause mouth breathing due to mouth opening, potentially causing sleep disturbance, Obstructive Sleep Apnea syndrome, and bruxism.^[3,4]^

Bruxism is defined by masticatory muscle activities that occur during sleep (characterized as rhythmic or non-rhythmic) and wakefulness (characterized by repetitive or sustained tooth contact and/or by bracing or thrusting of the mandible).^[5]^

Ethylogy is multifactorial and the main risk factors related to bruxism are gender, age, gene, mixed position, a lot of moving during sleep, sleeping with open mouth, snoring loudly, sleeping hours, sleeping anxiety, nervousness, passive smoking, high psychological reactions. with light on, cheek tone, emotional symptoms, mental health problems, birth weight, hyperactivity.^[6]^ In individuals with DS bruxism is often associated with sleep problems, snoring and obstructive sleep apnea.^[1]^

Stress has been reported to increase hypothalamus-pituitary-adrenal axis activity and alter the pattern of cortisol secretion, an important hormone used as a biomarker of psychological stress. Free cortisol determination can be easily measured in saliva. Stress sensitivity, as assessed by salivary cortisol, may be a psychological factor associated with bruxism.^[7]^

There are limited studies related to disease management in children. Treatment involves the control of anxiety and sleep, psychotherapy, physical therapy, and medications. Considering the high prevalence and difficulty in resolving this condition due to the lack of established treatment, any knowledge about bruxism is important and can assist in establishing better assessment and treatment strategies. The goal of treatment is to reduce physical, muscular and psychological tension. Therefore, a multidisciplinary approach involving physical therapy, pharmacotherapy, dentistry and psychology is required.^[8,9]^

Acupuncture has also been successfully used for the treatment of bruxism, achieving a reduction in the activity of the masseter and anterior temporal muscles as well as a reduction of anxiety.^[10]^ The stimulation of particular acupoints can promote muscle relaxation, thereby alleviating muscle spasms, inflammation and pain. Moreover, such stimulation leads to the release of hormones, such as cortisol and endorphins, thereby promoting an analgesic effect.^[11]^ Acupuncture point stimulation can be achieved with the use of needles, laser or electric current.^[12]^

Low Intensity Laser Therapy is a noninvasive and inexpensive treatment. Trigger point irradiation is an effective treatment for orofacial pain as well as reduction of swelling and hyperemia.^[13]^ However, there are no studies reporting the result of applying low intensity laser therapy on acupoints in children with DS and bruxism.

The aim of the proposed study is to analyze salivary levels of dopamine and cortisol and muscle activity before and after treatment with low-level laser therapy administered to acupoints in children with DS.

## Methods

2

### Study registration

2.1

The protocol for this study was registered ClinicalTrials.gov registration number: NCT04211870 on December 26, 2019. Available online: https://www.clinicaltrials.gov/ct2/show/NCT04211870.

### Ethics committee

2.2

A randomized controlled trial will be developed following the schedule shown in Figure 1. The study will be conducted in accordance with the norms governing research involving human subjects stipulated in Resolution n° 466/12 and 510/2016 of the Brazilian National Board of Health and has received approval from the Human Research Ethics Committee of Nove de Julho University (certificate number: 3.726.654). The guardians will sign a statement of informed consent and the children and adolescents will also sign a consent form. The invitation to participate in the study will be made after a survey of patients on the waiting list of the Integrated Health Clinic of the university).

**Figure 1 F1:**
[figure not shown]
SPIRIT figure as recommended by 2013 SPIRIT Statement.

### Participants

2.3

#### Inclusion criteria

2.3.1

(1)Children and adolescents with a diagnosis of DS(2)Four to seventeenyears of age(3)Bruxism, based on parental reports of the occurrence of grinding the teeth, incisal and/or occlusal and the questionnaire for the evaluation of bruxism

#### Exclusion criteria

2.3.2

(1)Use of muscle relaxant(2)Temporomandibular disorder(3)Undergoing other therapy for bruxism(4)Other associated neurological diseases(5)Cognitive deficit that impedes understanding the evaluations.

### Evaluations

2.4

All evaluations will be performed before starting the treatment protocol and at the last session.

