### Surface electromyography/diagnostic method (bitestrip)

2.8

*BiteStrip*is a disposable sensor that measures the activity of the masseter muscle during sleep.^[14]^

It can analyze contractions greater than 30% of maximum. Equipment parameters will be calibrated by [name], durantedevide positioning and produces a classification categorized into four scores, depending on events number quantified in a five-hour period (A or L = less tha 30 events; B = 31 to 60 events; C = 61 to 100 events; D = more than 100 events). All vonlunteers will be instructed to use BiteStripdurang one sleepnigth at beginning and the end of study. Parents/guardian will be Orientated regarding left temporal muscle location and device uses of following manufacture's instructions.

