### Allocation

2.10

The participants will be randomized to two groups with the aid of a randomization site (randomization.com): Group A – active photobiomodulation(n = 15); Group B – sham photobiomodulation(n = 15).

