#### Low-level laser therapy protocol

2.11.1

The same device (Laser DMC therapy EC) will be used for both groups. During sham treatment, however, the device will emit a guide light and sound, but no energy. Sessions will be held twice a week for six weeks (total: 12 session) using the parameters listed in Table 1. The participant will be seated comfortably in a quiet room with no sound interference. The tip of the laser will be covered in plastic wrap to avoid cross-contamination and for purposes of hygiene. The skin at the irradiation sites will be cleaned with gauze soaked in 70% alcohol.

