**Table 1 T1:**
[figure not shown]
Parameters.

A potentiometer will be used to measure the mean power of the equipment and therapeutic dose, ensuring safety to the participant and operator. Following the protocol suggested by Venezian et al^[13]^ and Carvalho et al.^[15]^(Fig. 2).

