### Statistical analysis

2.12

The data will be tabulated and treated using GraphPad PRISM version 7.0. The Kolmogorov-Smirnov test will be used to determine the normality of the data. Variables that fit the Gaussian curve will be expressed as mean and standard deviation. The ANOVA two-way will be used for comparisons between the groups, with the significance level set to 5% (*P* < .05). by one of the authors ([name], Applied Statistics Specialist).

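### The final evaluation is tied to the last treatment session and not to a time from baseline, so no clinic outcome is scheduled for a child who stops before session 12

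*Protocol article*

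**What the plan says.** Section 2.4 of the protocol article gives one timing rule for all measurements: "All evaluations will be performed before starting the treatment protocol and at the last session". The measurements described in the sections that follow are the NOT-S, head posture, salivary cortisol and dopamine, BiteStrip, and electromyography of the masticatory muscles.

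Section 2.11.1 fixes the course of treatment: "Sessions will be held twice a week for six weeks (total: 12 session) using the parameters listed in Table 1". On schedule, the last session is therefore session 12, in week 6.

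Section 2.8 times one of the measurements in other words: "All vonlunteers will be instructed to use BiteStripdurang one sleepnigth at beginning and the end of study". The end of the study is not defined.

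Section 2.10 gives the size of the trial: "Group A – active photobiomodulation(n = 15); Group B – sham photobiomodulation(n = 15". The Introduction states a before-and-after aim, to "analyze salivary levels of dopamine and cortisol and muscle activity before and after treatment with low-level laser therapy", and section 2.12 plans a two-way ANOVA between the groups at the 5% level.

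The text describes no intermediate or follow-up evaluation and none for a child who stops treatment. It does not say whether the last session means session 12 or the last one a child attends. The schedule figure (Figure 1) is not visible in the copy reviewed.

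**The concern.** An outcome schedule should apply to every randomised child in the same way, whatever happens to treatment. Here the timing of the final measurement depends on attendance. For a child who completes on schedule this makes no difference. For a child who stops, the rule schedules no clinic outcome; for a child who falls behind and makes up sessions, it moves the measurement past week 6.

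This is a matter of collection, not of analysis. An analysis plan can say who is analysed and how missing values are treated, but it cannot recover a saliva sample or an electromyography recording that was never taken. The aim is a before-and-after comparison, so a child without a post-treatment value contributes no observed change. Any analysis that includes that child must rest on assumptions that the data cannot test. If stopping is related to how the child is doing, and differs between the arms, the observed comparison is biased.

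**Working it through.** **Step 1. Read the rule both ways.**

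- *Last session means session 12.* A child who stops at, say, session 5 never reaches the event that triggers the evaluation. No NOT-S, posture, saliva or electromyography outcome is scheduled.
- *Last session means the last one the child attends.* The evaluation needs advance notice. Section 2.7 asks for 24 hours of preparation before saliva is collected, and section 2.8 needs a night at home with the device. A session known to be the last only in hindsight cannot supply these. If the evaluation were done, a value from week 2 or 3 would be pooled with week-6 values.

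Under either reading, a child who makes up missed sessions is measured after week 6, because the text states no window.

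**Step 2. Compare sections 2.4 and 2.8.** Section 2.4 places all evaluations at the last session. Section 2.8 places the BiteStrip, an overnight recording, at the end of the study. The two can coincide, but nothing in the text says that they do.

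**Step 3. Weight of one child.** With 15 per arm (section 2.10), 1/15 = 6.7% of an arm.

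**Step 4. Possible bias.** The article states no figure to reproduce here, and the inputs below are assumptions. For one arm:

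shift in completer mean = proportion lost × (completer mean − mean of those lost)

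| Assumed proportion lost | Assumed deficit of those lost | Shift |
|---|---|---|
| 10% | 0.5 SD | 0.10 × 0.5 = 0.05 SD |
| 20% (3 of 15) | 1.0 SD | 0.20 × 1.0 = 0.20 SD |

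If both arms lose similar children at similar rates, the shifts largely cancel in the between-group difference. The range applies when the loss is in one arm.

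For scale, the standard error of a difference between two means with 15 per arm is √(2/15) = 0.37 SD. The shift is therefore 0.05/0.37 = 0.14 to 0.20/0.37 = 0.54 of a standard error.

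**Step 5. How likely is it to arise?** The chance that at least one of 30 children stops early is 1 − (1 − d)^30, where d is the assumed stopping rate.

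| d | Expected number of 30 | Chance of at least one |
|---|---|---|
| 5% | 1.5 | 78.5% |
| 10% | 3 | 95.8% |
| 20% | 6 | 99.9% |

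**Step 6. Precision, for illustration.** With a two-sided 5% test, 80% power and the normal approximation, the detectable difference is (1.960 + 0.842) × √(2/n) SD.

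- n = 15 per arm: 2.802 × √(2/15) = 1.02 SD.
- n = 12 per arm (20% lost in both arms): 2.802 × √(2/12) = 1.14 SD.

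Power at 1.02 SD falls from 80% to 71%. The article gives no basis for its sample size, so this does not test that figure.

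**The case against.** The strongest reply is that section 2.4 is an ordinary summary of a pre/post design in a condensed article. Read with section 2.11.1, the planned last session already falls at week 6, which is the time proposed here. Nothing in the text forbids assessing a child who has stopped. Stopping and make-up sessions are not mentioned at all, and the schedule figure, which cannot be seen, may set visit times. Every input to the bias range is assumed, and even its upper end is well below the 1.02 SD that a trial of this size can detect.

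Much of this stands. The size is conditional, and the figure could change the reading of the text. It does not remove the point: the sentence in section 2.4 is a stated collection rule, and it coincides with week 6 only for children who complete on schedule.

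Two stronger readings are tempting, and the article supports neither.

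- *Children who stop have no safety evaluation.* Section 2.4 governs the outcome measurements. Collection of adverse events is not described for any child, and a condensed article commonly leaves it to the full protocol. The article does not discuss stopping for intolerance or harm.
- *Children who stop are excluded from the comparison.* Section 2.12 states no analysis set and no rule for missing data. Both may be in the full protocol or the analysis plan, which are not shown.

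Nor can it be said that every final measurement depends on attending session 12. The wording of section 2.8 may make the BiteStrip, which is worn at home, an exception.

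**Conclusion.** The point holds as one about the collection schedule. As written, the single stated post-baseline evaluation is anchored to a treatment event. No NOT-S, posture, saliva or electromyography outcome is therefore scheduled for a child who stops before session 12, the timing drifts for a child who makes up sessions, and the BiteStrip follows a separate, undefined time point.

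One unmeasured child is 6.7% of an arm. The possible shift of 0.05 to 0.20 SD in a completer mean rests wholly on assumed stopping rates (10% to 20% in one arm) and assumed deficits (0.5 to 1.0 SD). It shows what could happen and is not an estimate for this trial. The conclusion also assumes that the unseen schedule figure and full protocol do not already set a time-based visit for every child. This is an inexpensive improvement worth making, not a flaw that invalidates the design.

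**What to change.** In section 2.4, set the final evaluation at the end of week 6 counted from the first session, with a stated window, for every randomised child regardless of the number of sessions attended. In section 2.8, replace the end of the study with the same time point and window, so that the BiteStrip night falls with the other measurements.

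The change alters no treatment rule. It costs a revision of the wording, and it uses an evaluation visit already planned for each child. The small downside is that families who stopped must be asked to return, and some will decline. It therefore reduces missing outcomes but will not remove them.

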### Nordic orofacial test - screening (NOT-S) protocol

2.5

The participants will be analyzed using the NOT-S protocol developed by a work group formed at the Second Nordic Conference of Orofacial Therapy in Gothenburg, Sweden in 2002. The NOT-S has been translated and culturally adapted to Portuguese and can be downloaded free of charge at www.mun-hcenter.se. Thisprotocol consists of a structured interview and clinical examination, each with six domains. The following functions are addressed during the interview:

(1)sensory function,(2)breathing,(3)habits,(4)chewing and swallowing,(5)drooling and(6)dryness of the mouth.

The following functions are evaluated during the physical examination:

(1)face at rest,(2)nose breathing,(3)facial expression,(4)masticatory muscle and jaw function,(5)oral motor function and(6)speech Each domain has 1 to 5 items reflecting the complexity of the specific function.

The NOT-S will be administered individually by the same examiner in an empty room with the child sitting erect. The interview portion will be performed using the questions on the screening form. For the evaluation of orofacial dysfunction during the clinical examination, the participants will be asked to perform tasks for each item in accordance with the illustrated manual. Each item has criteria for the respective function. A “YES” response or task the meets the criteria for compromised function will be scored 1 point, indicating dysfunction in the respective domain. A “NO” response or task that does not meet the criteria will be scored zero. The total is the sum of the points of all domains and ranges from 0 to 12, with higher scores denoting greater orofacial disfunction.

### Head posture assessment

2.6

The clinical (visual) assessment of head posture will be performed using a posture grid. The participant will be instructed to stand with his/her natural posture. The natural balance of the head will be used to standardize the posture of each subject, who will be instructed to look forward with the gaze on the horizon. Semi-spherical polystyrene markers measuring 1.5 cm in diameter will be attached to the skin with double-sided adhesive tape at three anatomic points: the spiny process of the seventh cervical vertebra (C7), the manubrium of the sternum (A1) and the mental protuberance (MP). Photographs will be taken of each participant in right-side view.

### Evaluation of salivary cortisol and dopamine levels

2.7

The participants and caregivers will receive verbal and written instructions to avoid any physical activity, the ingestion of substances with alcohol or caffeine, soft drinks, tea, corticoids, and chewing gum in the 24 hours before the collection of the saliva. Saliva samples will be collected using polyester swabs (Salivette, Sarstedt, Germany), which will be refrigerated immediately after collection. The swab will be placed under the tongue and the participant will be instructed to move it around the oral cavity until it becomes soaked with saliva (stimulated saliva. The swabs will be centrifuged at 3500rpm for 5 minutes. The supernatant will be collected and stored at −80°C.

Cortisol will be determined using an enzyme-linked immunosorbent assay (ELISA) (Salimetrics, State College, PA). Dopamine will also be determined using an ELISA kit (Dopamine Research ELISA BA E-5300). All kits were used following the manufacturer's instructions. The optical density of the samples was measured in a spectrophotometer at 450 nm.

### Surface electromyography/diagnostic method (bitestrip)

2.8

*BiteStrip*is a disposable sensor that measures the activity of the masseter muscle during sleep.^[14]^

It can analyze contractions greater than 30% of maximum. Equipment parameters will be calibrated by [name], durantedevide positioning and produces a classification categorized into four scores, depending on events number quantified in a five-hour period (A or L = less tha 30 events; B = 31 to 60 events; C = 61 to 100 events; D = more than 100 events). All vonlunteers will be instructed to use BiteStripdurang one sleepnigth at beginning and the end of study. Parents/guardian will be Orientated regarding left temporal muscle location and device uses of following manufacture's instructions.

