### Evaluation of electromyography of masticatory muscles

2.9

The electrical activity resulting from the activation of the muscles will measured using the six-channel TMJOINT electromyograph (BTS Engineering) with an bioelectrical signal amplifier, wireless data transmission and disposable bipolar surface electrodes (Ag/AgCl, Medical Trace) measuring 10 mm in diameter. The EMG signal will be amplified with a 2000-fold gain and filtered within a frequency of 20 to 450 Hz. The impedance and common rejection mode ratio of the equipment are >1015 Ω/0.2 pF and 60/10 Hz 92 dB. The data will be collected and digitized at 1000 frames/second using the BTS MYOLA software program.

After cleaning the skin with 70% alcohol to diminish the impedance, the surface electrodes will be attached to the belly of the muscle in the region of greatest tone (determined with the volunteer performance moderate intercuspation). The inter-electrode distance will be 20 mm center to center, as recommended by the European Society Recommendations for Surface Electromyography (SENIAM). A reference electrode will be placed on the left wrist of the volunteer to impede the interference of external noise.

The muscles analyzed will be the masseter (right and left) and anterior temporal (right and left). Evaluations will be performed under 4 conditions:

(1)at rest,(2)during habitual maximum intercuspation with a strip of Parafilmbetween the molars to determine maximum voluntary contraction (MVC) of the muscles studied,(3)during habitual chewing (isotonic contraction) and (IV) during maximum intercuspation (isometric contraction) without parafilm. All readings will be performed 3 times with a two-minute rest period between readings. The collection time will be 15 seconds with the muscle at rest, 5 seconds during MVC and 10 seconds during isotonic and isometric contraction. A metronome set at 60 beats per minute will be used for the reading during habitual chewing.

The EMG signal collected during chewing will be rectified and normalized by the mean of the signal followed by the calculation of the root mean square (RMS) using a 500-ms moving window without overlap. The data will be normalized by the highest RMS obtained during MVC.

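### The overnight BiteStrip outcome is defined on the masseter, but the only site instruction in section 2.8 points parents to the left temporal muscle

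*Protocol article*

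**What the plan says.** The Methods part of the abstract states: "Masseter muscle activity during sleep will be assessed by BiteStrip". Section 2.8 opens in the same sense, saying that the device "is a disposable sensor that measures the activity of the masseter muscle during sleep". It then gives the detection threshold, "It can analyze contractions greater than 30% of maximum", and a four-level score (A or L, B, C, D) from the number of events in a five-hour period. The device is worn for "one sleepnigth at beginning and the end of study".

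The section closes with the instruction to families: "Parents/guardian will be Orientated regarding left temporal muscle location". The same sentence goes on to the use of the device according to the manufacturer. No other site or side is given for the device in the article. The masseter is named as what the device measures, never as where it goes.

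Section 2.9, which covers the clinic electromyograph, states: "The muscles analyzed will be the masseter (right and left) and anterior temporal (right and left".

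**The concern.** The outcome definition names one muscle and the site instruction names another. A surface sensor reports on the muscle beneath it, so its position determines what the score means. If families follow the location they are taught, a result reported as masseter activity would describe the temporal muscle.

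This matters because BiteStrip is the only instrument in the article that records muscle activity during sleep, in a trial whose population is defined by possible sleep bruxism. Bruxism at entry rests on parental report and a questionnaire (2.3.1). NOT-S is an interview and clinical examination (2.5). The clinic electromyography covers rest, maximum voluntary contraction, chewing and intercuspation (2.9). None of these can stand in for an overnight recording taken at an unintended site.

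**Working it through.** The article gives no figure to reproduce on this point. The check is a comparison of statements, plus one count.

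**Muscle named, by place**

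| Place | Muscle | Role of the statement |
|---|---|---|
| Abstract, Methods | Masseter | What BiteStrip will assess |
| 2.8, opening | Masseter | What the device measures |
| 2.8, last sentence | Left temporal | Location taught to parents/guardians |
| 2.9 | Masseter and anterior temporal, each right and left | Muscles recorded by the clinic electromyograph |

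**Step 1. Could the two names mean the same site?** No. Section 2.9 lists them as distinct muscles.

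**Step 2. Does section 2.9 explain the temporal reference in 2.8?** No. It concerns a different device used under waking test conditions.

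**Step 3. Is the last sentence of 2.8 about placement?** It says that parents are oriented to a location; it does not literally say that the sensor is attached there. But it joins the location to the use of the device in one sentence, and no purpose other than placement is evident. Placement is therefore the natural reading, though an inferred one.

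**Step 4. What would depend on the site?** Events are contractions above 30% of maximum. Over the temporal muscle, both the contractions and the maximum would belong to that muscle, and so would the A/L to D category.

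**Step 5. How many recordings?** Section 2.10 gives 15 + 15 = 30 children. Section 2.8 gives one night at the beginning and one at the end. 30 × 2 = 60 recordings. This is the number that would be affected if every family followed the instruction. It does not measure the distortion, which cannot be sized from the article.

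**The case against.** The strongest reply is that this is a wording slip. Section 2.8 is visibly garbled in several places, two statements say masseter, and one clause says temporal. The same sentence also refers to the manufacturer's instructions, which are not shown and may fix the actual site. This stands in part: the article does not show that the sensor will in fact be worn over the temporal muscle. It does not remove the inconsistency. If the manufacturer's instructions name another site, parents would receive two conflicting directions.

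A second reply is that one muscle and one side are named for every child, in both arms and on both nights, so the comparison between arms is not biased. That stands. The harm lies in what the outcome represents.

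A third is that BiteStrip is nowhere designated primary, and that the muscle-activity aim is also served by the clinic electromyography, which records both muscles. That is correct and limits the weight of the point, but the clinic recording is not a sleep measure.

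Two stronger readings are tempting and are not supported:

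- A reader might infer that families place the sensor with no staff member able to correct the site. The article does not say so. Section 2.8 contains a garbled sentence that appears to describe calibration by a named person during device positioning. It does not say whether that person checks the site.
- A reader might infer that sites will vary between families or between the two nights, adding error to the before/after change. The text names a single site for everyone, so this is conjecture.

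**Conclusion.** The concern holds as an internal inconsistency. The abstract and the opening of 2.8 define the outcome on the masseter, while the only site instruction orients parents to the left temporal muscle. Followed as written, it would put the trial's only overnight muscle recording, up to 60 recordings, on a muscle other than the one the outcome names.

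This rests on reading the last sentence of 2.8 as a placement instruction. It also assumes that the unseen manufacturer's instructions do not override that sentence. If siting is uniform, the randomised comparison remains internally consistent but the result is mislabelled. The article supports no claim of bias between arms, lost power or a change to the sample size.

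The point should be settled before any recording is made, because a night recorded over an unintended muscle cannot be reassigned afterwards.

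**What to change.** Reconcile the abstract, the opening of 2.8 and the last sentence of 2.8 so that the outcome definition and the instruction to parents name the same muscle and one fixed side. If the outcome definition stands, that muscle is the masseter. Check this against the manufacturer's instructions first, since the article alone cannot establish which site the device requires. If the temporal muscle was intended, the outcome definition has to change instead.

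State that the same muscle and side are used on both nights, and record the site used for each recording.

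The cost is a short correction to the text and to whatever instruction the families receive, plus one data field per recording.
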